### Allocation Not Applicable

#### Blinding

The study is an open-label study, as blinding of the participants is neither possible for single-arm studies nor in fasting interventions.

### Data Collection

The measures and cut offs for testing feasibility and also the assessment tools for the other research questions have been described above. The endpoints in the form of questionnaires or patient reported outcomes (PROs) are recorded via the StudyU app^
62
^ and electronic Case Report Form (eCFRs) via lime survey. The StudyU platform (https://studyu.health) allows intervention studies to be performed digitally while adhering to data protection regulations.

The StudyU applications are written in Flutter, an open-source framework. The source code is publicly available on GitHub and studies on the StudyU platform comply with ethical principles and international regulations, particularly the GDPR (European Union) 2016/679. Each participant is assigned an anonymous user account with a random ID assigned to the participant, eliminating the need for identifiable user profiles or app logins and enabling easy and user-friendly daily health parameters collection. This allows an individual and statistical analysis of the intervention’s effect, which is then reported back to participants to strengthen their confidence.

The patient’s consent must explicitly cover the collection and processing of personal data. Personal data and test results are protected. Participants are informed that their disease-related data and test results will be stored pseudonymously at the respective study centers and used for scientific evaluations. Data will not be shared with third, not actively involved parties. Data collected via StudyU will be stored on a server at HPI in anonymized form and published anonymously via the platform. All other data will be deleted after 10 years.

### Data Monitoring

The data monitoring committee consists of a medical doctor, a study nurse and a bioinformatics expert. The committee monitors the study visit schedules at both centers and the assessment including patient-reported outcomes. The 2 recruiting centers are required to report any changes to the study visit schedules or deviations from the study protocol to the monitoring committee. In the event of protocol deviations, the committee will report to the study coordinators. The Data Monitoring Committee is free from competing interests. Further details on the functioning of the committee can be obtained by emailing the corresponding author.

### Harms

Fasting should be discontinued immediately if serious adverse events occur (eg, neurological deficits as an indication of hyponatremia). In that case, patients will be given immediate medical care or referred to emergency care.

Each adverse event must be documented in detail if, in the opinion of the investigator, there is a causal relationship with the intervention. The documentation includes the type of event, severity, onset, duration, causality and changes for the study. Related signs and symptoms should be summarized as a single disease. The “adverse events study patient” form is available for documentation purposes. All adverse events must be tracked until they subside or stabilize.

Serious adverse events will be reported to the study coordinator and principal investigator as soon as they become known, that is, within 24 hours. The principal investigator, in close collaboration with the data monitoring committee and the study coordinator, may decide to discontinue the study, either due to adverse or serious adverse events attributable to the study intervention, or for the reasons mentioned in the section “exclusion criteria,” or because not enough patients could be recruited. Interim analyses are not conducted as no adverse health effects are expected.

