## Introduction

Breast cancer is the most frequently diagnosed cancer and the leading cause of death among women worldwide.^
1
^ Advances in early detection, diagnostic precision and therapeutic approaches have significantly improved survival rates, leading to an increasing number of women undergoing long-term adjuvant therapies.^
2
^ Among these, aromatase inhibitors (AIs) are the standard therapy for postmenopausal women with early-stage, hormone receptor-positive breast cancer, which accounts for over 80% of all breast cancer cases.^3,4^ Typically prescribed for up to 10 years, AIs significantly reduce recurrence risk and improve survival outcomes.^5,6^ However, despite these therapeutic benefits, their use is frequently associated with adverse effects, particularly aromatase inhibitor-induced arthralgia (AIA) and aromatase inhibitor-induced musculoskeletal symptoms (AIMSS), affecting up to 74% of treated patients.^7,8^ These symptoms often lead to an increase in psychosomatic distress and physical disability, followed by poor adherence and therapy discontinuation, which results in higher rates of breast cancer recurrence and all-cause mortality.^
9
^

AIMSS/AIA often presents as arthralgia, osteopenia and an increased risk of fractures.^10
[Bibr bibr11-15347354261426272]-12^ These manifestations are largely attributed to the hypoestrogenic state induced by AIs, which elevates pro-inflammatory cytokines and interleukins, stimulating bone resorption and impairing bone formation.^13,14^ Understanding the pathophysiological mechanisms of AIMSS/AIA is essential for developing effective therapeutic strategies; however, these mechanisms remain only partially understood, as estrogen deficiency not only affects bone health but also influences joint pain, inflammation, and immune function. Estrogen normally exerts chondroprotective and antinociceptive effects, and its absence results in increased pain perception and autoimmune dysregulation.^8,15,16^ Radiological evidence further supports these findings, showing increased fluid in joints and tendon sheaths, which contributes to pain and inflammation.^17
[Bibr bibr18-15347354261426272]-19^

Many chronic diseases are aggravated by diet induced inflammation. Caloric restriction (CR) has been shown to reduce inflammation and oxidative damage while enhancing insulin sensitivity and energy metabolism.^20

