Criteria for discontinuation are defined to ensure participant safety and to appropriately document feasibility. Although prolonged fasting is generally considered safe in supervised settings, participants may discontinue the fasting intervention at any time in case of intolerance. If a participant consumes more than the permitted caloric intake on a given day, this deviation will be documented as part of the feasibility assessment, but the participant will not be withdrawn from the study for this reason alone.

Adverse events (AEs) and severe adverse events (SAEs) are continuously documented according to the Common Terminology Criteria for Adverse events (CTCAE), Version 5.0 (U.S. Department of Health and Human Services, 2017). Should relevant (S)AEs occur—such as marked dizziness, clinically concerning weight loss (eg, BMI dropping below 20 kg/m^2^), or other symptoms that raise safety concerns—the study physician will evaluate the situation and decide whether continuation of the fasting protocol is appropriate. In cases of doubt, the fasting intervention will be discontinued as a precaution. Participants will, however, remain enrolled in the study unless safety considerations explicitly require study removal. All discontinuations of the fasting intervention and the underlying reasons will be recorded in detail.

Personal doubts regarding the ability to adhere to the intervention are a major factor influencing compliance. Although the adherence cannot be comprehensively monitored in the outpatient setting, close supervision and support will be provided. The online group meetings can help build a sense of community, potentially affecting compliance in a positive way.

Ongoing medical treatments or changes to them will be documented on each study visit. For some medications (eg, diuretics, antihypertensives, oral antidiabetics and others) a dose adjustment may be necessary, as fasting has effects on metabolism and therefore various biochemical parameters. For more information on possible and necessary changes in medication, please refer to Supplemental File 2.

The fasting method as used in our intervention is based on the protocol established by the Charité University Outpatient Clinic for Naturopathy, Immanuel Hospital Berlin, and has already been evaluated in various clinical studies.^25,30,40^

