#### Additional Parameters

In order to describe the patient collective as accurately as possible, the following additional parameters will be recorded. At baseline sociodemographic data and medical history will be documented. Before starting the fasting intervention, participants are asked to report on their dietary habits by using a standardized questionnaire, please refer to Supplemental File 4. Besides dietary habits and the intake of stimulants, personal experiences with fasting as well as physical activity behavior are also recorded. Possible changes in dietary habits initiated by the fasting and nutritional counseling are documented at *t*2 (Supplemental File 4).

At each study visit (*t*0, *t*1 and *t*2) anthropometric data and adverse events are documented, and blood samples are offered on an optional basis. Anthropometric data include weight, height, BMI, heart rate, blood pressure, waist circumference and Bioelectrical impedance analysis (BIA) measurement. BIA will be used to assess for example, fat-free mass (FFM), skeletal muscle mass (SMM), total body water (TBW), intracellular and extracellular water (ICW/ECW), and phase angle (PA). To ensure reliable measurements, all assessments follow our institutional SOP, which includes standardized conditions such as: no food intake for at least 3 to 4 hours before measurement, adequate hydration the day before, avoidance of alcohol and caffeine for 24 hours and intense physical activity for 12 hours, and voiding the bladder immediately beforehand. Because the first BIA assessment occurs before the start of fasting and the second after the 3 day recovery period, these requirements can be met. The optional blood tests are collected primarily to provide participants with individualized feedback on metabolic and nutritional parameters at the end of the intervention. In addition, together with the anthropometric assessments, they serve as an additional evaluation of participants’ nutritional and general health status to ensure appropriate medical supervision and counseling before and during the fasting intervention. Blood biomarkers include fasting plasma glucose (FBG), gamma-GT, triglycerides (TG), high- and low-density lipoprotein-cholesterol (HDL, LDL), ferritin, CRP and insulin. Fatty liver index (FLI) and HOMA Index are calculated. The specimens are not stored for any further use.

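### Harms requires a detailed adverse event record only after the investigator has judged the event causal, so onset and a recorded causality assessment are not required for events judged unrelated; the stop rules for serious events also need aligning

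*Protocol article*

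**What the plan says.** **The conditional rule.** Harms states: "Each adverse event must be documented in detail if, in the opinion of the investigator, there is a causal relationship with the intervention". It then lists the content of that record: "The documentation includes the type of event, severity, onset, duration, causality and changes for the study".

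**The unconditional rules.** Four other statements carry no causality condition.
- Interventions: "Adverse events (AEs) and severe adverse events (SAEs) are continuously documented according to the Common Terminology Criteria for Adverse events (CTCAE". The version named is 5.0.
- Additional Parameters: at each of the three visits "anthropometric data and adverse events are documented".
- Harms: "All adverse events must be tracked until they subside or stabilize".
- Harms, for serious events: "Serious adverse events will be reported to the study coordinator and principal investigator as soon as they become known", with a limit of 24 hours.

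Interventions adds a record for one kind of consequence: "All discontinuations of the fasting intervention and the underlying reasons will be recorded in detail".

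**Use of attribution.** Harms allows the principal investigator, with the data monitoring committee and the study coordinator, to end the study because of adverse or serious adverse events attributed to the intervention.

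**Stopping the fast.** Harms calls for fasting to stop at once when a serious adverse event occurs, and gives neurological deficits pointing to hyponatremia as an example. Interventions says that after relevant events, abbreviated (S)AEs, the study physician decides whether fasting continues, with a precautionary stop when in doubt. Its examples are marked dizziness and BMI falling below 20 kg/m². That section spells out SAE as severe, where Harms says serious.

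**The concern.** A causality assessment is normally an entry in an adverse event record. Here it is the condition for making the full record. An event that the investigator considers unrelated need not have its start date written down, nor the reasoning or grade of the causality opinion.

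This matters more than usual for three reasons. First, the study is single-arm and open-label, so there is no concurrent group whose event rate could expose misattribution. Second, every participant takes an aromatase inhibitor, of which the Introduction says "their use is frequently associated with adverse effects". A rival explanation is always at hand. Third, attribution feeds a decision, because study discontinuation on safety grounds refers to events attributed to the intervention. A record that is thin exactly where attribution was negative is a weak basis for checking that decision, or for planning the harms section of the confirmatory trial.

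On stopping the fast, two centres need one instruction. Read literally, a serious event that the physician is confident can be managed while fasting continues falls under an immediate stop in one section and under discretion in the other.

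**Working it through.** No calculation applies. The check takes the six fields that Harms lists and asks, for an event judged unrelated, whether any other sentence in the article requires each one.

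| Field listed in Harms | Required elsewhere for an event judged unrelated? | Source |
|---|---|---|
| Type | Yes, implied by CTCAE documentation | Interventions |
| Severity | Yes, implied by CTCAE grading | Interventions |
| Duration | Largely: every event is followed to resolution or stabilisation, which gives its end, though not a recorded length | Harms |
| Changes for the study | In part: the reason is recorded wherever fasting was stopped | Interventions |
| Onset | Not stated | – |
| Causality assessment | Not stated | – |

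Of 6 fields, 2 (type, severity) are covered and 2 (duration, changes for the study) are partly covered. That leaves 6 − 2 − 2 = 2 with no other stated requirement: onset and causality.

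**Does the gap stop at non-serious events?** No. The condition in Harms applies to each adverse event. A serious event judged unrelated gains reporting within 24 hours, but the article does not say that onset and causality are then recorded.

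**Do the visits supply onset?** Only coarsely. The visit after the programme follows 2 preparation + 7 fasting + 3 refeeding = 12 days. An event noted at that visit without an onset date cannot be assigned to preparation, fasting or refeeding, and those are the periods on which a causality judgement would turn. Continuous documentation may yield dates in practice, but the text does not require it.

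**Is any planned criterion affected?** No. The feasibility criteria under Primary Outcome rest on recruitment, retention, adherence (at least 5 of 7 days, with infeasibility if more than 30% fail) and assessment completion (at least 75%). None uses onset or causality of adverse events.

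**Stop rules side by side.**

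| | Harms | Interventions |
|---|---|---|
| Term | serious | severe, abbreviated (S)AE |
| Example | neurological deficits | marked dizziness, BMI below 20 kg/m² |
| Action | immediate stop | physician decides; stop if in doubt |

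The examples suggest two tiers of event, but the abbreviation covers both tiers and neither section refers to the other.

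**The case against.** The strongest reply is that what remains is detail at the level of a form. Harms names a dedicated adverse event form that is not shown and may already hold a start date and a causality box for every event, and a journal article need not repeat it. That would be decisive if the article were merely silent. It is not: it states a rule, and the rule makes the detailed record conditional. A centre following the text as written would be entitled to leave those entries blank.

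A second reply is that the filter cannot operate without an opinion on every event, so a bare CTCAE entry implies that the event was judged unrelated. This is fair as far as it goes, and a yes/no screen before a graded assessment is not circular. But an implied negative cannot be told apart from an assessment that was never made.

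Third, timing is not wholly lost. Pain and fatigue are rated daily in the StudyU app from one week before to one week after the intervention, and pain, function and fatigue instruments are completed at each visit. For those symptoms the course around the fast can be looked at again. That stands, and it limits the harm to other kinds of event.

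Fourth, the stop rules may well be meant for different events, and both lean towards stopping. That also stands. It makes this part a matter of clarification.

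A reader might go further and infer that unrelated events go unrecorded, that their duration is lost, or that a judgement of unrelated can never be revisited. The documents support none of these: all events are documented and followed up, and daily symptom data exist.

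**Conclusion.** The point holds in a limited form and is minor. As written, Harms makes the detailed record depend on a prior, unblinded causality opinion. Onset and a recorded causality assessment are then not required for any event judged unrelated, serious or not. The all-cause count, CTCAE grades, follow-up, 24-hour reporting of serious events and discontinuation reasons all survive, and no feasibility criterion is invalidated. What is weakened is the ability to re-examine negative attributions in a single-arm study whose safety stop refers to attributed events.

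The number of events affected cannot be stated, because the article gives neither an adverse event rate nor the share expected to be judged related. The conclusion assumes that sites follow the stated rule; if the form already collects both fields for every event, only the wording is at fault.

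The two stop rules differ in term and in action. A reader might call this a flat contradiction. The differing examples allow a reading in which they cover different events, so the supportable statement is that the text does not say which rule applies to which event.

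**What to change.** Replace the conditional sentence in Harms with wording such as: *Each adverse event is documented with type, CTCAE grade, seriousness, onset, end or outcome, and changes for the study, whatever its suspected cause; the investigator's causality assessment is recorded as a separate field.*

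In Interventions, expand SAE as serious, limit the physician's discretion to non-serious adverse events, and refer to the immediate-stop rule in Harms for serious ones. The clinical investigators should confirm that this is the intended division; if it is not, they should state the single rule they want.

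The cost is one sentence in Harms, one clause and one word in Interventions, and a few more entries on the existing adverse event form. Recruitment began in November 2023, so this would be a clarification or amendment. For events already entered without onset or causality, the fields would have to be completed from source notes where those allow, and the report should say where they do not.

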## Discussion

This is the first study to investigate the feasibility of prolonged therapeutic fasting on AIMSS/AIA among breast cancer patients receiving aromatase inhibitor treatment. While the evidence for nutritional interventions in cancer care continues to grow, research specifically addressing fasting in the context of AIMSS/AIA remains sparse. To date, various nutritional interventions have demonstrated positive effects on treatment tolerance and symptom burden, particularly as complementary approaches to the conventional treatments for breast cancer patients. Based on this positive evidence, our study seeks to address the gap in clinical research in this unique context by exploring the feasibility and preliminary effects of fasting.

### Strengths

Fasting has been shown in other studies to be an effective, cost-efficient, and safe intervention for breast cancer patients and a way of introducing healthy habits.^61,63^

While our intervention specifically focuses on fasting (consisting of vegetable juices and broths, max. 350 kcal/day) many of the described molecular mechanisms have been extensively studied in the context of calorie restriction (CR). These mechanisms include the downregulation of proinflammatory cytokines,^64,65^ macrophage polarization toward an anti-inflammatory M2 state, and the promotion of autophagy.^66
[Bibr bibr67-15347354261426272]-68^ Emerging evidence suggests that similar physiological responses are activated during fasting.^
69
^ Moreover, fasting improves gut barrier integrity, reduces bacterial toxin absorption, and fosters protective bacteria in the microbiota.^70,71^ These systemic effects may contribute to reducing inflammation and enhancing overall wellbeing in breast cancer patients. Our study design incorporates validated fasting protocols supported by continuous counseling, ensuring qualified and accessible supervision. The short duration of the fasting intervention and the outpatient care with online meetings and the group environment are designed to maximize participant compliance through easy accessibility and peer support, laying the groundwork for potential translational implementation in everyday clinical practice. Nutritional counseling at *t*1 helps to address the common challenge of maintaining long-term behavioral changes.

One of the distinguishing features of this intervention is that it not only emphasizes fasting but also integrates important components such as mindfulness and exercise, thus offering a more holistic approach. Physical activity benefits patients by improving quality of life and mindfulness,^
26
^ reducing anxiety, depression, and fatigue, and enhancing cardiorespiratory fitness and muscular strength.^72,73^ Exercising while fasting can optimize glucose regulation, enhance lipid oxidation, and reduce systemic inflammation, collectively improving key health outcomes. The body draws on stored glycogen, fats and proteins as energy sources^
74
^ and switches toward fat oxidation and lipolysis, supporting energy needs through gluconeogenesis and ketogenesis.^74
[Bibr bibr76-15347354261426272]-76^ Previous studies have also described positive effects on the gut microbiota, including bowel motility and intestinal blood flow. By strengthening the intestinal barrier, the mucosal immune cells help to reduce low-grade inflammation and maintain overall gut integrity.^
77
^ Furthermore, in fibromyalgia patients, low-speed exercises minimize the impact on joints, enhance microcirculation and promote the elimination of oxygen free radicals.^
78
^ By reducing peripheral nociceptive input, they disrupt the pain cycle, leading to a more effective pain management.^
78
^

Additionally, this study captures a comprehensive range of exploratory outcomes, including anthropometric data and patient-related outcomes such as quality of life and fatigue. These measurements, complemented by electronic data monitoring via the StudyU app, enable the collection of complete datasets and provide feedback to participants on their individual progress, motivating them to hold on to lifestyle changes. The flexibility and user-friendly design of the StudyU app enhance participant engagement while adhering to rigorous data protection standards.

By incorporating validated tools such as scales, questionnaires and blood biomarkers, our study creates a basis for identifying potential outcome measures for future studies. BIA measurements allow a better insight into potential effects of fasting on body composition.

Observing feasibility in this pilot study will lay the groundwork for a confirmatory follow-up study, including a control group and adjusted endpoints, to provide more robust and conclusive evidence.

